**ABSTRACT**

Cervical cancer and HIV are intersecting epidemics that both disproportionately affect low-income women; the impact of the socioeconomic disparity and biologic synergy of these two diseases is seen dramatically in Kenya, where cervical cancer is the most common cancer killer. HIV-infected women are at increased risk for the development of cervical precancer and cancer, develop more aggressive lesions and are affected at younger ages. Although screening for and treatment of precancer has reduced the incidence of cervical cancer to close to zero in resource-rich countries, strategies are costly and not available in most resource-limited countries. Novel testing and treatment methods that can be carried out in low-resource settings are urgently needed to prevent cervical cancer in these settings, especially among HIV-infected women. Using a cross-sectional study design, we propose to test two potentially low-cost and effective cervical cancer screening methods: **visual inspection with acetic acid** (VIA) and **protein biomarkers** expressed in the presence of cervical dysplasia, neither of which have been well-studied in HIV-infected women. We will also randomize a small subset of women to undergo VIA compared to **Visual Inspection with Lugol's Iodine (VILI**) to compare the test characteristics of these two screening exams. In addition, remarkably little is known about the potential **impact of the presence, diagnosis and treatment of HPV-related dysplasia on HIV genital shedding, a major risk factor for HIV transmission**. To explore the impact of the presence, diagnosis and treatment of HPV-related cervical dysplasia on HIV-1 in genital secretions, we will compare the levels of HIV-1 RNA found in the cervicovaginal secretions of women with no evidence of cervical dysplasia to levels in women with high-grade cervical dysplasia. We will also compare the levels of HIV-1 RNA prior to and after cervical biopsy as well as up to 14 weeks after standard treatment for cervical dysplasia using loop electrosurgical excision procedure (LEEP). Results from this study will inform the prioritization and design of safe, effective and low-cost cervical cancer screening and prevention programs for HIV-infected women in resource-limited settings.

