We will sequentially recruit and enroll eligible women for all specific aims. There will be three separate consent forms (Appendix A, B and L). Screening and informed consent for participation in the studies involving VIA or VILI, colposcopy and specimen collection (S.A. 1, 2 and 3) will take place in a private gynecologic exam room prior to pelvic exam. Because satisfactory visual exam or clinical evidence of cervical or pelvic infection will only become evident after exam, participant numbers will be assigned after VIA and colposcopy. Women who are unsure about enrollment and would like time to consider will be given an information sheet (Appendix C) and may return for enrollment at a later date. VIA in these women will be deferred until their next visit. Eligibility and informed consent for the post-LEEP genital shedding sub-study will take place at a clinical visit, prior to their LEEP procedure. Women will be given an information sheet specific to this part of the study, in addition to the normal clinical materials in use that explain the LEEP procedure (Appendix D).

Statistical Considerations and Sample Size Calculation

**Specific Aim 1:** To calculate a sensitivity of 75% with a confidence interval of 5% in both directions and a two-sided alpha of .05, we will need to complete sequential VIA and colposcopy in ***1800* women**.^83^

To determine a specificity of 80%, with a confidence interval of 5% in both directions and a two-sided alpha of .05, we calculate that we will need to examine 400 women. Because the scientific outcome of specificity is most important, we will use the estimate of 1,800 women (900 VIA and 900 VILI to account for laboratory and sampling error) to power our study.

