Data Storage: The study will be conducted within the existing clinic settings in the Nyanza Province. Data will be collected from the electronic medical record and on study-specific forms (Appendices F and G). Study data will be included as part of the patient’s medical file and maintained in locked file cabinets within the clinic. Data will be abstracted to computers by data entry clerks and managed by the assigned data manager at each site. Abstracted data will be labeled by unique study ID only. A file correlating study ID and medical file number will be kept in separate password-protected Excel computer file and accessible only to the core research team. Additionally, all study computers are password protected and kept in locked offices within the clinics.

Statistical Analysis:

Statistical analysis for all specific aims will be carried out using STATA and SPSS software.

**Specific Aim 1**: The goal of specific aim 1 is to calculate the sensitivity, specificity and predictive values of VIA and VILI for CIN2/3, with colposcopy as the gold standard. Colposcopy will be performed on every participant, regardless of screening result, to avoid verification bias.^92^ To calculate the sample size for this study, we assume that the prevalence of CIN2/3 among HIV-infected women at FACES will be 7%, as has been seen in the cervical cancer screening program at FACES.^78^ Sample size calculations will be based on prior estimates of VIA sensitivity, as these are more prevalent and therefore have more precision.

Sensitivity: Previous studies have shown that VIA has a sensitivity of 60-86%^39, 40, 91, 93-97^ for detection of CIN2/3 among healthy women, which is comparable to the sensitivity of cervical cytology and would be an acceptable test characteristic for this setting. In order to determine sensitivity, we will construct a 2 x 2 table, and divide the number of women with a true positive VIA result (i.e. those with disease diagnosed by colposcopy and VIA) by the number of true positive VIAs plus the number of false negative VIAs. Specificity: Specificity values for VIA range from 64 to 94% for the detection of CIN2/3.^39, 40, 91, 98, 99^ To determine specificity of VIA, we will divide the number of participants with true negative VIA (i.e. has no disease diagnosed colposcopically) by the number of true negative tests plus the number of false positive tests.

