**Pathology Reading ($4,000)**

Pathology specimens will be read by a trained pathologist at KEMRI, with whom there is an established relationship for FACES and the cervical cancer screening program. From our current rate of positive colposcopies and detection of CIN2/3, we have estimated that approximately 500 specimens will be read at $8 per specimen for this study. The UCSF pathologist has agreed to provide a second read of the prepared specimens at no extra fee. Total: 500*8=$4,000.

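### Aim 1 promises sensitivity to within ±5 points from 1,800 women; at the plan's own 7% prevalence and 900 women per visual test it delivers about ±11 points

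*Protocol*

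**What the plan says.** In the protocol, Statistical Considerations and Sample Size Calculation, Specific Aim 1, the target is set "To calculate a sensitivity of 75% with a confidence interval of 5% in both directions and a two-sided alpha of .05", and the number of women given for it is 1,800. For a specificity of 80% with the same ±5 points, the number given is 400.

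The section then explains the choice: "Because the scientific outcome of specificity is most important, we will use the estimate of 1,800 women". The full sentence also fixes the allocation: "we will use the estimate of 1,800 women (900 VIA and 900 VILI to account for laboratory and sampling error) to power our study".

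Under Study Design, each participant has VIA or VILI, not both, followed or preceded by colposcopy. Swabs for p16 and HR-HPV are taken from every woman. The sample-size paragraph for Specific Aim 2 says that Aim 2b reuses the Aim 1 numbers.

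Under Statistical Analysis, Specific Aim 1, the plan says that for the sample size "we assume that the prevalence of CIN2/3 among HIV-infected women at FACES will be 7" per cent. The same section defines sensitivity with true positives plus false negatives as the denominator, and specifies exact binomial confidence limits.

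The Abstract describes the VIA/VILI comparison differently: the investigators will "randomize a small subset of women".

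**The concern.** The precision of a sensitivity estimate depends on the number of diseased women, not on the number screened. At 7% prevalence, 1,800 women contain about 126 with CIN2/3, and 900 contain about 63. Neither number supports ±5 points around 75%.

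Two separate things go wrong. First, 1,800 does not follow from the stated inputs, even for a single test. Second, those 1,800 are shared between two tests done in different women, with no change to the stated precision.

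Estimating sensitivity and specificity is the purpose of Aim 1. A reader of the sample-size section would expect a sensitivity interval of about 70% to 80%. The design would give about 62% to 85%, which covers nearly all of the 60% to 86% range that the protocol quotes from earlier studies of VIA. Aim 2b takes over the same numbers, so it takes over a weaker form of the same shortfall.

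**Working it through.** **Inputs.** From the sample-size section for Aim 1: sensitivity p = 0.75, half-width d = 0.05, two-sided alpha 0.05 (z = 1.96), 1,800 women split 900/900, specificity target 0.80 ± 0.05. From Statistical Analysis, Aim 1: prevalence 0.07, denominator diseased women only, exact limits. The protocol refers to a published nomogram for the calculation. I assume that it rests on the usual one-proportion precision formula.

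**Attempt to reproduce 1,800.**
- Diseased women needed: z² × p(1−p) / d² = 1.96² × 0.75 × 0.25 / 0.05² = 288.
- Women to screen: 288 / 0.07 = about 4,116 for one test. With exact limits, 306 diseased women are needed: 306 / 0.07 = about 4,371.
- The stated 1,800 is not reproduced. Other readings at 7% do not give it either. A one-sided z of 1.645 gives 2,899. Sensitivities from 60% to 90% give between 1,976 and 5,268. A half-width of 7.5 points comes close, at 1,829.
- The formula returns 1,800 at a prevalence of about 16% (288.1 / 0.16 = 1,801), which the plan does not state.

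**Delivered precision for sensitivity at 7%.** The Wald half-width is 1.96 × √(0.1875 / number of cases).

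| Women on the test | CIN2/3 cases | Wald | Exact (example) |
| --- | --- | --- | --- |
| 900 (VIA or VILI) | 63 | ±10.7 | 47/63: 62.1% to 84.7%, about ±11.3 |
| 1,800 (all on one test) | 126 | ±7.6 | 94/126: 66.1% to 81.9%, about ±7.9 |

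**How far this depends on prevalence (Wald).**

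| Prevalence | 900 women | 1,800 women |
| --- | --- | --- |
| 5% | ±12.7 | ±8.9 |
| 7% | ±10.7 | ±7.6 |
| 10% | ±8.9 | ±6.3 |
| 16% | ±7.1 | ±5.0 |

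With 900 women per test, ±5 points would need a prevalence of about 32% (288 / 900).

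**Specificity.** The target needs 1.96² × 0.8 × 0.2 / 0.05² = 246 women without disease, or 246 / 0.93 = about 265 in total. The stated 400 is therefore more than enough. With 900 × 0.93 = 837 disease-free women per test, the half-width is 1.96 × √(0.16 / 837) = ±2.7 points.

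**The stated rationale.** The plan attributes 1,800 to sensitivity and 400 to specificity, and then adopts 1,800 on the ground that specificity matters most. The reason and the number do not belong together. Nor does dividing 1,800 between two tests make allowance for laboratory or sampling error, since it halves the number on each test.

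**The abstract.** If VILI goes to a small subset only, VIA receives between 900 and 1,800 women, so its half-width lies between ±7.6 and ±10.7 points. VILI would then be worse than ±10.7. Neither reading reaches ±5 for either test.

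**The case against.** The strongest reply is that this does limited harm. Aim 1 is estimation with no decision rule tied to ±5 points. The confidence limits will be reported, so the true imprecision will be visible, and nothing is biased. The plan names specificity as the more important outcome, and specificity is estimated better than its target. All of that stands. It does not rescue the planning statement, because no part of the protocol sets a looser sensitivity target for the split sample.

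The word specificity in the rationale may be a slip for sensitivity. If so, correcting that word would mend the sentence, but 1,800 would still fall short of the sensitivity target.

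Three stronger readings are tempting, and the document does not support them.
- A reader might infer that the protocol works with two prevalences. The budget expects that "approximately 500 specimens will be read", and the Aim 2 section gives a 57% predictive value of positive colposcopy for CIN2/3. Then 500 × 0.57 = 285, and 285 / 1,800 = 15.8%, close to the back-calculated 16%. But the budget line is a rounded cost estimate that counts specimens. It does not say that there is one per woman, or which procedures they come from. At 7%, 126 / 0.57 gives about 221 women with positive colposcopy. The gap between 221 women and 500 specimens is at most a query.
- A reader might conclude that the VIA-versus-VILI comparison fails its power. With 63 cases per arm it is imprecise, but the protocol sets no power target or detectable difference for it.
- A reader might take the 900/900 split as governing and the abstract as wrong. The document does not say which holds.

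**Conclusion.** The claimed precision is wrong as written. On the protocol's own inputs (sensitivity 75%, prevalence 7%, 900 women per visual test, exact limits), each sensitivity estimate will carry about ±11 points, more than twice the stated ±5. Reaching ±5 would take about 4,116 women per test.

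The ±11 figure applies to VIA and VILI under the 900/900 split. For p16 in Aim 2b the figure is about ±8 with exact limits. That assumes the assay is available in all 1,800 women and that its sensitivity is also near 75%, for which the plan gives no separate value. The specificity target is met for both visual tests.

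The result is not delicate: at any prevalence from 5% to 16%, 900 women per test miss ±5 points. Only about 16% prevalence together with all 1,800 women on one test would meet it. The plan does not state that prevalence, and its allocation rules that out for the visual tests.

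**What to change.** Change the wording of the Aim 1 sample-size section as follows.

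- Replace the ±5-point claim for sensitivity with the delivered precision, using the exact limits that the analysis section specifies: about ±11 points per visual test (about 63 women with CIN2/3) and about ±8 points for p16 if measured in all 1,800 (about 126). Give specificity as about ±3 points per visual test (about 837 women without CIN2/3).
- State the prevalence used next to the calculation. If it is not 7%, give the value and its source, and recompute.
- Correct the sentence that justifies 1,800 by specificity, so that the reason matches the number.
- Reconcile the abstract's description of the randomised subset with the 900/900 split, and quote the precision for whichever allocation holds.
- Optionally, explain how the 500 budgeted specimens relate to the expected number of women biopsied.

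This needs no extra participants or procedures. The cost is a less favourable precision statement. If ±5 points is truly required, the alternative is about 4,116 women per visual test, and the sponsor would have to choose that knowingly.

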**OBJECTIVES:**

General:

We seek to establish the link between the presence, diagnosis and treatment of cervical dysplasia and HIV genital shedding. We also seek to establish the sensitivity and specificity of three resource-appropriate screening methods, VIA, VILI and p16^INK4a^ biomarker testing, for cervical dysplasia.

Specific (Aims):

**Aim 1:** **To calculate the sensitivity, specificity, and the positive and negative predictive values of visual inspection of the cervix after application of 3-5% acetic acid (VIA) and visual inspection with Lugol’s Iodine (VILI) for the diagnosis of cervical intraepithelial neoplasia grade 2 and grade 3 (CIN2/3) in HIV-infected women.** HIV-infected women enrolled in care at the FACES clinics in western Kenya will undergo VIA or VILI and colposcopy with directed biopsy as indicated. The colposcopy will be used as the reference standard, allowing for calculation of sensitivity, specificity, positive and negative predictive value of VIA and VILI.

Hypothesis 1: VIA and VILI will have test characteristics validating their use as a screening test for cervical dysplasia among HIV-infected women in resource-limited settings.

**Aim 2: To define the quantitative value of a biochemical assay for p16^INK4a^ that predicts cervical neoplasia with the greatest sensitivity and specificity among HIV-infected women using a receiving operating characteristic (ROC) curve.**

**Aim 2a: To compare the sensitivity and specificity of the p16^INK4a^ biochemical assay with that of HR-HPV testing.** HIV-infected women enrolled in care at the FACES clinics in western Kenya will undergo specimen testing for p16^INK4a^ and HR-HPV, followed by colposcopy with directed biopsy as indicated.

**Aim 2b: To calculate the sensitivity and specificity of the p16^INK4a^ biochemical assay for the detection of CIN2/3 using colposcopy as the gold standard.** HIV-infected women will have p16^INK4a^ specimens collected prior to colposcopy. Diagnosis for positive p16 will be based on the ROC curve cut-off determined in the pilot study, with colposcopy as the reference standard as above.

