**Specific Aim 2:** We based our sample size calculations for this aim on the following calculations: a sample of 42 women with positive results and 60 with negative results will achieve 90% power to detect a difference of 0.1 between the histology result and the AUC for the p16^INK4a^ assay using a two-sided z-test at a significance level of 0.05.^84^ Histology is the gold standard for diagnosis of CIN, which would give it an AUC of 1.0; a 0.1 difference mean an AUC for p16^INK4a^ of 0.90, which would make it an excellent diagnostic tool. Our power to detect even greater difference with this sample size would be even greater. We will enroll ***60* women with negative colposcopies, and *140* women with positive colposcopic exams**. The positive predictive value of a positive colposcopy at FACES is approximately 57% for CIN2/3 and 89% of any diagnosis of CIN.^85^ A sample of 140 women with positive colposcopic exams will ensure that we have an adequate number of women with the positive result of interest (CIN2/3) to achieve our specific aim, and potentially enough women with lower levels of CIN to obtain preliminary information regarding test characteristic among this group. In order to calculate the specificity and sensitivity (SA 2b), we will use the sample sizes calculated above for specific aim 1.

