We propose a ***cross-sectional*** study to evaluate this specific aim. Each participant will undergo a VIA or VILI with specimen collection for p16^INK4a^ and HR-HPV and colposcopy by a different clinician during a single clinic visit. The study clinician performing the colposcopy will be blinded to the results of the VIA or VILI. For women in the VILI arm, the colposcopy will be performed first in order to eliminate any interference with colposcopy interpretation from the iodine staining. Biopsy decisions will be made at the time of colposcopy, but deferred until after the VILI. Any woman with cervical lesions suspicious for dysplasia seen at the time of colposcopy will undergo biopsy. Colposcopy will be used as the reference standard for presence or absence of CIN2/3, with biopsy results being the final diagnosis when available. Women with a normal colposcopy without biopsy will be considered to have no disease.Specific Aims 1, 2, 2a and 2b)

We propose a **prospective cohort** study using a subset of women identified from the cross-sectional study in Specific Aims 1 and 2a to evaluate specific aim 2c during a one-year follow-up visit. We will recruit women for this follow-up study who participated in the pilot p16^INK4a^ ELISA study (Aim 2a) and had normal colposcopy or CIN1. In a single visit, each participant will undergo a VIA with specimen collection for p16^INK4a^ and HR-HPV followed by colposcopy and biopsy if needed.

We propose a ***case-control*** study to measure and compare the presence and quantity of HIV-1 RNA in the cervicovaginal specimens of women with biopsy-confirmed CIN2/3 (cases) and age-matched women without evidence of cervical disease as measured by negative VIA (controls). We will compute the odds ratio for HIV-1 detection and compare log transformed mean viral loads between cases and controls. (Specific Aim 3)

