**ETHICAL CONSIDERATIONS**

Human Subjects Involvement and Characteristics

The study described in this proposal will involve a total of around 1,800 HIV-infected women receiving care at the FACES clinics in Kisumu, Kenya. Women will be included in the study for the cross-sectional validation study if they are: 1) 25 years or older 2) not pregnant 3) accept cervical cancer screening 4) have a satisfactory Visual Inspection with Acetic Acid (VIA). Participants will be recruited for the prospective follow-up study (Specific Aim 2c) if they meet the above criteria, and were found to have normal colposcopy or CIN1 upon initial screening with p16^INK4a^ biomarker measurement. Participants will be recruited for the prospective post-LEEP HIV-1 shedding study if they meet the above criteria, have undergone LEEP for treatment of CIN2/3 and agree to remain abstinent for three days prior to each of the follow-up visits. To participate in any of these study activities, women must be willing and able to participate, be able to sign or mark a consent form, and speak one of the languages into which the consent form and data collection instruments have been translated, including English, D’Luo and Kiswahili.

Sources of Materials

Data for this study will be collected from several sources. Clinical and demographic data will be obtained through chart reviews and physical examination. We will also obtain clinical information from the colposcopic examinations. Information from the colposcopy and if performed, biopsy, will be entered into the participants’ medical records as it will be used to direct clinical care. We will also obtain cervical specimens for p16^INK4a^ and HR-HPV testing and vaginal wick specimens for women in the post-LEEP HIV-1 shedding study. These will be obtained solely for research purposes, and will therefore not be entered into the participant’s medical record. All data collection will take place in a private study room.

Potential Risks

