In addition to sensitivity and specificity, we will calculate the positive and negative predictive values of VIA. Studies have shown a PPV of VIA for CIN2/3 to range from 9-27% in HIV-negative women.^97, 100, 101^ To calculate the PPV in our study, we will divide the number of participants with a positive VIA by the number of participants found to have CIN2/3 on biopsy. VIA has been shown to have a negative predictive value (NPV) of 91-99.5% in HIV-negative women.^102^ To calculate the NPV, we will divide the number of participants with a negative VIA by the number of participants with no evidence of disease at colposcopy, either by visual impression or a negative biopsy result. Confidence limits for estimates of sensitivity, specificity, PPV and NPV will be exact, based on the binomial distribution.

Finally, we will compare the test characteristics between the two screening modalities using a McNemar’s test of proportions.

**Specific Aim 2**: To determine the cut-off value for the p16^INK4a^ biochemical assay that will provide the highest sensitivity and specificity for the detection of CIN2/3, we will construct a Receiver Operating Characteristic (ROC) curves using the results of the ELISA-based assay and the histology specimens. An ROC curve will allow us to plot the True Positive Rate (TPR) and the False Positive Rate (FPR) for various values of the p16^INK4a^ assay. As TPR is equivalent to the sensitivity of a test, and 1-FPR is the specificity, the graphical representation, as well as the calculated Area Under the Curve will allow us to determine the cut-off value for p16^INK4a^ to define a “positive test” with the highest sensitivity and specificity.

We will compare the absolute differences in sensitivity and specificity for detection of CIN2/3 of p16^INK4a^ and HR-HPV using the Mann-Whitney U test. The values of p16^INK4a^ will be determined from the ROC curves in Specific Aim 2. The sensitivity and specificity of the HR-HPV tests will be calculated as below:

- To calculate **sensitivity**, we will divide the number of women with a true positive test by the number of true positives plus the number of false negative HR-HPV testing.
- To calculate **specificity**, we will divide the number of participants with no disease diagnosed colposcopically (true negatives) by the number of true negative plus false positive HR-HPV tests.

Confidence limits for estimates of sensitivity and specificity will be exact, based on the binomial distribution.

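### The protocol does not separate the women who set the p16 cut-off from those in whom Aim 2b evaluates it, so the Aim 2b sensitivity is modestly optimistic

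*Protocol*

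**What the plan says.** - **Where the cut-off comes from.** Objectives, Aim 2b: a positive p16 result "will be based on the ROC curve cut-off determined in the pilot study".
- **Where it is evaluated.** Statistical Considerations and Sample Size Calculation, Specific Aim 2: "In order to calculate the specificity and sensitivity (SA 2b), we will use the sample sizes calculated above for specific aim 1". Under Specific Aim 1 that size is fixed: "we will use the estimate of 1,800 women", split into 900 VIA and 900 VILI.
- **The pilot as planned.** The Specific Aim 2 paragraph enrols 60 women with negative and 140 with positive colposcopy. It puts the predictive value of a positive colposcopy for CIN2/3 at about 57%.
- **How pilot and cohort relate.** Study Design covers Aims 1, 2, 2a and 2b with one cross-sectional study and one visit, p16 being collected from each participant. The Aim 2c women, who took part in the pilot, are recruited "using a subset of women identified from the cross-sectional study in Specific Aims 1 and 2a". Ethical Considerations says the study "will involve a total of around 1,800 HIV-infected women".
- **Intervals.** Statistical Analysis, Specific Aim 2: "Confidence limits for estimates of sensitivity and specificity will be exact, based on the binomial distribution".

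The protocol does not say that pilot women are left out of Aim 2b, and it does not say outright that they are included.

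**The concern.** Aim 2b reads as a second stage: fix a threshold in the pilot, then measure how it performs. That is an independent test only in women who did not help to choose the threshold. A cut-off picked to do well in a given set of cases looks better in those cases than in new ones. If pilot cases are pooled into Aim 2b, its sensitivity inherits part of that optimism. Exact binomial limits treat the cut-off as if it had been set beforehand.

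The error always favours p16. HR-HPV is read at a manufacturer's fixed cut-off and gains no such advantage, and Hypothesis 2 expects p16 to do better. Readers would also take the full number of cases as validation when only the non-pilot cases serve that purpose.

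**Working it through.** **Inputs.** N = 1,800, target sensitivity 75% ± 5 points, 140 positive and 60 negative colposcopies, and 57% predictive value (all from the sample size section). Prevalence comes from Statistical Analysis, Specific Aim 1: "we assume that the prevalence of CIN2/3 among HIV-infected women at FACES will be 7" per cent. About 500 biopsy specimens are expected (Budget Justification, Pathology Reading).

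**1. The plan's 1,800.** Cases needed = 1.96² × 0.75 × 0.25 / 0.05² = 288.
- At 7% prevalence: 288 / 0.07 = about 4,116 women, so 1,800 does not reproduce.
- At 16%: 288 / 0.16 = about 1,800, so it does.
- The budget points the same way: 500 × 0.57 = 285 cases, and 285 / 1,800 = 15.8% (assuming one specimen per woman).

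The protocol therefore carries two prevalences, 7% stated and about 16% implied, and the overlap has to be shown for both.

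**2. Share of cases in the planned pilot.** Pilot CIN2/3 = 140 × 0.57 = 79.8, about 80.

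| Prevalence | Cases in 1,800 | Pilot share | Cases outside pilot |
| --- | --- | --- | --- |
| 5% | 90 | 89% | 10 |
| 7% (stated) | 126 | 63% | 46 |
| 10% | 180 | 44% | 100 |
| 16% (implied) | 288 | 28% | 208 |

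**3. Share of non-cases.** Pilot non-cases = 200 − 79.8 = 120.2. At 7% prevalence, 120.2 / (1,800 − 126) = 7.2%. At 16%, 120.2 / (1,800 − 288) = 7.9%. Of all women, 200 / 1,800 = 11%.

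**4. The pilot as reported.** The Specific Aim 2c paragraph gives 190 normal colposcopies and 55 CIN1 (245 women), which does not match the planned 60 and 140, and gives no CIN2/3 count. Two guesses show how open this is:
- If CIN2/3 were 7% of an unselected pilot: 245 / 0.93 × 0.07 = about 18 cases, or 15% of 126.
- If CIN1 is scaled by the predictive values of 89% (any CIN) and 57%: 55 / (0.89 − 0.57) × 0.57 = about 98 cases, or 78% of 126.

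Both are assumptions and neither should be used.

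**5. Size of the bias.** Simulation with an assumed binormal marker; the cut-off maximises sensitivity plus specificity (Youden) in 80 cases and 120 non-cases. Apparent minus true sensitivity within the pilot is about 2.9, 3.6 and 4.1 points at AUC 0.90, 0.80 and 0.70. Pooling dilutes it by the pilot share:
- 63% overlap (× 80/126): about 1.8, 2.3 and 2.6 points.
- 28% overlap (× 80/288): about 0.8, 1.0 and 1.1 points.

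At AUC 0.80 and 63% overlap, mean pooled sensitivity is 74.0% against 71.8% in non-pilot women. At AUC 0.90 it is 83.0% against 81.2%. Pooled specificity is too high by only 0.1-0.2 points. The nominal 95% exact interval for pooled sensitivity covers about 93% at 63% overlap.

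**6. Precision.** The 95% half-width at 75% sensitivity is 1.96 × √(0.1875/n): ±7.6 points with 126 cases and ±12.5 with 46.

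**The case against.** **The nesting is inferred.** Aim 2b borrows the Aim 1 sample size, and the Aim 2c paragraph speaks of the pilot as already done, so a reader could picture a separate earlier group. This stands as a caution. But one cross-sectional design, a total of about 1,800, and the description of pilot women as drawn from that cross-sectional study all point to nesting, and no second population is described.

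**The effect is small.** A bias of 1 to 2.6 points sits inside a half-width of 7.6 points with 126 cases. That is true and limits the weight of the point. The bias is nonetheless systematic, and correcting it takes only analysis code.

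**The exact-limits sentence follows the HR-HPV formulas**, so applying it to Aim 2b is a reading. It is, however, the only interval method that the Aim 2 analysis gives for sensitivity and specificity.

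**Optimism correction is often left to an SAP.** Agreed for the technique. Which women make up the Aim 2b estimate is a design matter that the protocol leaves unresolved.

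**Stronger readings that the documents do not support.**
- A reader might infer that Aim 2b tests the cut-off mainly on the women who set it. Pilot women are 11% of participants and about 7% of the non-cases behind specificity. They are a majority of cases at the stated 7%, but not at the implied 16%.
- A reader might count on 46 cases enrolled after the cut-off is fixed. No section dates the cut-off. The time frame ends enrolment in July-September 2011 and runs specimen processing to October-December 2011, so that group could be much smaller or empty.
- Comparing exact limits of 83-94% (113/126) with 76-96% (41/46) shows what dropping pilot women costs. It does not show that the pooled interval is too narrow; the evidence for that is the coverage of about 93%.

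**Conclusion.** The point holds as a lack of separation between the women who set the p16 cut-off and those who test it, with a modest effect on sensitivity and almost none on specificity. With the planned pilot, the reused share of CIN2/3 cases is 63% at the stated 7% prevalence and 28% at the implied 16%. For the pilot as reported it is unknown. Pooled Aim 2b sensitivity is too high by about 2-2.6 points in the first case and about 1 point in the second. Exact limits fall slightly short of 95% (about 93% at 63% overlap).

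This rests on the inferred nesting, the planned 60/140 pilot, the 57% predictive value, every CIN2/3 having a positive colposcopy, and an assumed binormal marker with a Youden cut-off. It concerns Aim 2b and not the Aim 2a comparison with HR-HPV inside the pilot.

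**What to change.** In the Specific Aim 2 sample size paragraph and the Specific Aim 2 analysis:

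1. State that pilot women are part of the 1,800, if that is so, and give the pilot's actual CIN2/3 count.
2. Compute Aim 2b sensitivity and specificity in all women. Take the optimism correction and confidence limits from a bootstrap that repeats the cut-off choice in the resampled pilot women.
3. Report sensitivity in non-pilot women separately, as the check independent of the cut-off, with its actual number of cases. Quote about 46 only for the planned pilot at 7% prevalence.
4. Do not base specificity on non-pilot women alone. The pilot over-samples abnormal colposcopies: at 7% and 57%, 126 / 0.57 = about 221 are expected and the pilot takes 140. Removing them would make specificity look too good.

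The cost is a slightly lower reported sensitivity, a wider interval, a few sentences and some analysis code. No extra participants or tests are needed.
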